### Sample size calculation

For both phases, the sample size calculation was based on the effect size for a significant and clinically meaningful reduction in patient-reported pain (ie, the primary outcome measure, the Brief Pain Inventory (BPI))^54^ and calculated using G Power V.3.1.9.6.

Phase One: using a repeated measures analysis of variance (ANOVA; between factors) sample size calculation with an effect size of d=0.64,^54^ power=0.95, alpha=0.05, considering two treatment arms and three measurements timepoints (ie, pre-intervention and post-intervention, and follow-up), the required sample size is 24 patients. However, to account for a 10% drop out (as guided by previous ADMR publications^50 55 56^), a minimum of 28 patients will be recruited (n=14 per study arm).

Phase Two: using a repeated measures ANOVA (between factors) sample size calculation with an effect size of d=0.64,^54^ power=0.95, alpha=0.05, two treatment arms, and four measurements timepoints (ie, pre-intervention, end-week 1 intervention, end-week 2 intervention and post-intervention), the required sample size is 22 patients. However, to account for a 10% drop-out, 26 patients will be recruited (n=13 per study arm).

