### Phase Two RCT

A 3-week RCT (resembling actual inpatient rehabilitation duration at DMRC) will compare the efficacy of the most clinically acceptable BFR pressure from Phase One to standard/conventional UK Defence Rehabilitation residential rehabilitation practice on physiological mechanisms underpinning changes in pain modulation and rehabilitation outcomes. It is hypothesised that the BFR-RT group will have greater reductions in pain, and increases in function, when compared with usual care alone.

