### Statistical methods and analysis

Descriptive data will be reported as the mean and SD for continuous variables and frequency statistics for non-continuous variables. Prior to statistical analysis, normality tests will establish data distribution; if data are non-normally distributed, transformation and the use of non-parametric statistical analysis tests will be employed. All tests will be two-sided, and alpha significant will be set a priori p<0.05. A between-subjects and within-subjects ANOVA will be used to assess the effect of the intervention on all outcome variables. Any statistically significant two-way interactions will be followed up using post hoc analysis with Bonferroni corrections to account for multiple comparisons. The magnitude of any differences will be presented using 95% CI and Cohen’s D for effect size.

Supporting analysis of the primary outcome will include a per-protocol analysis including patients with compliance >80% to intervention. In addition to the primary adjusted analysis, the unadjusted mean differences between groups will be reported using t-test, reporting 95% CI. Study participant flow will be recorded and reported as per CONSORT guidelines. Analysis will be conducted on a pairwise case basis. Therefore, all missing data will be reported, and patterns investigated. Sensitivity analysis will be conducted using multiple imputation techniques to assess the effect of missing data on primary outcomes. Post-intervention adverse events between groups will be analysed using Fisher’s exact test. All analysis will be conducted using SPSS.

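### The stated 95% power belongs to the group effect averaged over all visits, baseline included, and not to the between-arm difference in change that the trial hypothesises

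*Protocol article*

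**What the plan says.** Under Sample size calculation, Phase One is sized "using a repeated measures analysis of variance (ANOVA; between factors) sample size calculation" and Phase Two "using a repeated measures ANOVA (between factors) sample size calculation", both "calculated using G Power V.3.1.9.6". The Phase One inputs are "power=0.95, alpha=0.05, considering two treatment arms and three measurements timepoints", with an effect size given as d=0.64. Phase Two uses the same effect size, power and alpha with four timepoints. In both phases the pre-intervention visit counts as one of the timepoints. The required totals are 24 and 22, raised for dropout to 28 and 26.

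The Study aims section states the question as a difference in change. Phase One expects a greater hypoalgesic response at high pressure. Phase Two expects that "the BFR-RT group will have greater reductions in pain, and increases in function, when compared with usual care alone".

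Statistical methods and analysis plans an ANOVA with between-subject and within-subject factors, and its rule for what happens next is: "Any statistically significant two-way interactions will be followed up using post hoc analysis with Bonferroni corrections to account for multiple comparisons". It does not say which F test in that ANOVA is the primary test of efficacy.

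**The concern.** A repeated-measures ANOVA with two arms and several visits has a group main effect and a group-by-time interaction. The routine used here powers the first, which compares the arms on their average over all visits. A hypothesis of greater reduction is a statement about the second, or about a contrast of change from baseline. The tests differ in degrees of freedom and noncentrality, so power for one is not power for the other.

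Counting the pre-intervention visit also weakens the main effect as a measure of treatment. Randomised arms are expected to be equal at that visit, so a treatment difference of d afterwards enters the average as 2d/3 in Phase One and 3d/4 in Phase Two.

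What is at stake is how a null result is read. In Phase Two (Experimental intervention), the choice of pressure turns first on whether the Phase One BPI difference is statistically significant. The Phase Two efficacy reading rests on the same kind of test. If either is null, readers will give it the weight of a trial with 95% power.

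**Working it through.** **Inputs from the article.** N=24 with m=3 visits (Phase One); N=22 with m=4 visits (Phase Two); effect size 0.64; two-sided alpha 0.05; 1:1 allocation.

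**Assumptions.** The article gives no correlation between visits (ρ) and no visit-by-visit pattern. I take SD 1 at each visit, compound symmetry, ρ=0.5, no difference before the intervention and d at every later visit. Power is from the noncentral F distribution.

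**1. Reproduce the plan.** For the between factors routine, λ = f²·N·m / (1+(m−1)ρ), with 1 and N−2 df.
- Phase One, f=0.64: λ = 0.4096·24·3/2 = 14.75, power 0.956. N=22 gives 0.938, so 24 is the smallest even total.
- Phase Two, f=0.64: λ = 0.4096·22·4/2.5 = 14.42, power 0.950. N=20 gives 0.928, so 22 is the smallest even total.

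Both printed totals match. They match together only for ρ of about 0.44 to 0.50. The software's interaction routine with the same nominal inputs would return 10 and 8, so the group main effect is what was powered.

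**2. Separate out the d/f issue.** With two equal arms f = d/2, so f=0.64 means d=1.28, while the printed d=0.64 means f=0.32. At f=0.32 the between factors routine itself gives λ = 3.69 and 3.60, power 45% and 44%. That loss has nothing to do with which effect is tested.

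**3. Interaction.** λ = (N/4)·Σ(δₜ−δ̄)²/(1−ρ), with m−1 and (N−2)(m−1) df. The sum is (2/3)d² in Phase One and (3/4)d² in Phase Two.
- d=1.28: λ = 6·1.092/0.5 = 13.11 and 5.5·1.229/0.5 = 13.52; power 89% and 86%.
- d=0.64: λ = 3.28 and 3.38; power 33% and 29%.

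**4. Main effect under the same pattern.** λ = (N/4)·m·δ̄²/(1+(m−1)ρ), with 1 and N−2 df and δ̄ = 2d/3 or 3d/4.
- d=1.28: λ = 6.55 and 8.11; power 69% and 77%.
- d=0.64: λ = 1.64 and 2.03; power 23% and 27%.

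**5. Single contrast of change** (mean of later visits minus the pre-intervention visit, between arms). λ = (N/4)·d²/v, where v = (1−ρ)·m/(m−1), which is 0.75 and 0.667. At ρ=0.5 this gives the same λ as step 3, but on 1 and N−2 df.
- d=1.28: power 93% and 94%.
- d=0.64: power 41% and 42%.

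**6. Range over ρ** (interaction power, Phase One / Phase Two, N=24/22).

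| ρ | d=0.64 | d=1.28 |
|---|---|---|
| 0.3 | 24% / 21% | 76% / 71% |
| 0.5 | 33% / 29% | 89% / 86% |
| 0.7 | 51% / 46% | 99% / 98% |
| 0.9 | 95% / 93% | above 99% |

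**The case against.** **The interaction is not declared primary.** This is true. The article says only that the ANOVA assesses the intervention effect, adds unadjusted t-tests, and gives a follow-up rule for interactions. That the interaction carries the efficacy claim is inferred from that rule and from the hypotheses. The point does not hang on the inference, though: with equal arms at baseline and ρ=0.5, the main effect does not reach 95% either (step 4).

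**The loss to 33% and 29% is mostly a different error.** This stands. A reader might infer that choosing the wrong routine cost the trial about two thirds of its power. At d=0.64 the routine accounts for the fall from 45% to 33% and from 44% to 29%; the rest is d entered as f. At the effect size that generated the totals, the fall is from about 96% and 95% to 89% and 86%, or to 93.5% and 91.9% if all 28 and 26 patients complete.

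**The trial need not be too small for the interaction.** This also stands. At the same nominal f the interaction routine asks for fewer patients, and at ρ=0.5 the interaction has more power than the main effect. At d=1.28 and ρ=0.7 it exceeds 95%. The article's test-retest coefficients for the BPI (0.90 to 0.96) suggest that ρ could be above 0.5, although reliability is an upper guide and not the correlation across an intervention. Values that high would not, however, reproduce the printed totals.

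**The main effect does respond to treatment.** A reader might infer that the routine is valid only if the arms differ equally at every visit, which treatment could not produce. Its noncentrality depends only on the average difference. Treatment does move that average, but the baseline visit dilutes it.

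**The limitations are acknowledged.** The article warns of type I and II errors from small samples and calls Phase One a pilot. That softens the consequence but leaves the printed 0.95 uncorrected.

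**Conclusion.** The concern holds in a limited form. The printed 0.95 is the power of the visit-averaged group main effect, as both the named routine and the exact reproduction of 24 and 22 show. It is not the power of a test of difference in change, which is what the hypotheses describe.

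With equal arms at baseline, a constant difference afterwards and ρ=0.5, neither F test in the planned ANOVA reaches 95% at 24 and 22 patients, even with the generous reading d=1.28. The interaction falls short by about 6 and 9 percentage points.

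The documents do not support a fixed shortfall or a fixed direction, because ρ and the pattern over visits are not given. Nor do they support attributing the 33% and 29% to the choice of routine. The point should be corrected, but it does not invalidate the design.

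**What to change.** Keep 28 and 26 patients.

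In Statistical methods and analysis, name one primary effect that measures the between-arm difference in change in the BPI. It can be either the omnibus group-by-time interaction or a 1-df contrast of change from the pre-intervention visit. These are different tests with different power (steps 3 and 5), so the text should name one and not treat them as interchangeable. State that a group main effect that averages in the pre-intervention visit will not be counted as evidence of efficacy.

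In Sample size calculation, replace the between factors calculation with the power of the named effect at the planned numbers. Give the assumed difference at each visit and the assumed correlation, with a range over that correlation, in place of the unqualified 0.95. Settle the d/f labelling in the same pass, since every restated figure depends on it.

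The cost is one re-run of the power calculation and rewording in two sections, with no extra patients or visits. The drawback is a less favourable printed power.

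### The stated d=0.64, 95% power and totals of 24 and 22 cannot all hold: both totals arise when 0.64 is entered as Cohen's f, which equals d=1.28

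*Protocol article*

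**What the plan says.** The section Sample size calculation applies one approach to both phases. The software is named ("calculated using G Power V.3.1.9.6"), and so is the routine with its effect size. For Phase One: "using a repeated measures analysis of variance (ANOVA; between factors) sample size calculation with an effect size of d=0.64". For Phase Two: "using a repeated measures ANOVA (between factors) sample size calculation with an effect size of d=0.64". Power is 0.95 and alpha 0.05 in both.

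- Phase One, three time points: "considering two treatment arms and three measurements timepoints (ie, pre-intervention and post-intervention, and follow-up), the required sample size is 24 patients". Allowing for 10% drop-out, 28 are recruited.
- Phase Two, four time points: "the required sample size is 22 patients". Allowing for 10% drop-out, 26 are recruited.

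No Cohen's f and no correlation among the repeated measures is given. The section Statistical methods and analysis specifies a between- and within-subjects ANOVA and continues: "Any statistically significant two-way interactions will be followed up using post hoc analysis". It reports effect sizes as Cohen's d.

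**The concern.** A two-group comparison with a standardised difference of 0.64 would normally need far more than 24 patients for 95% power, and averaging three or four correlated measurements closes only part of that gap. The likely cause is a mix-up of scales. The between-factors routine expects f, which for two equal arms is half of d, so typing 0.64 into the f field doubles the planning effect.

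The stake is more than a label. Under Experimental intervention for Phase Two, the pressure is chosen first on the Brief Pain Inventory (BPI). If the BPI difference is not significant, the choice passes to the Lower Extremity Function Scale, and failing a difference there, to a default. With power well below 95%, that fallback is used more often than a reader of the sample size section would expect, even when a BPI difference of the stated size exists.

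**Working it through.** **Inputs from the protocol article.** Two arms, 1:1 allocation (Randomisation and blinding procedure); two-sided alpha 0.05 (Statistical methods and analysis); m=3 or 4 time points, d=0.64 and power 0.95 (Sample size calculation). **Assumed:** the correlation rho, which is not stated. I take 0.5, the G*Power default, and then vary it from 0 to 0.9.

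**Formula for the named routine.** Non-central F with 1 and N−2 degrees of freedom and lambda = N·f²·m / (1+(m−1)·rho). For two equal arms f = d/2.

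**Step 1: reproduce the stated totals, with f=0.64 and rho=0.5.**
- Phase One: lambda = 24 × 0.4096 × 3 / 2 = 14.75, power 95.6%. At N=22 it is 93.8%, so 24 is the smallest even total.
- Phase Two: lambda = 22 × 0.4096 × 4 / 2.5 = 14.42, power 95.0%. At N=20 it is 92.8%, so 22 is the smallest even total.

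Both published figures are matched exactly at one common correlation. f=0.64 corresponds to d = 2 × 0.64 = 1.28.

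**Step 2: use the stated d, so f=0.32 and rho=0.5.**
- Phase One: lambda = 24 × 0.1024 × 3 / 2 = 3.69, power 45.1%. 95% power needs N=88.
- Phase Two: lambda = 22 × 0.1024 × 4 / 2.5 = 3.60, power 43.9%. 95% power needs N=82.
- If all recruited patients are analysed (28 and 26), power is 51.5% and 50.8%.
- At N=24 and 22, 95% power is available only for d of about 1.26 and 1.28.

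**Step 3: vary the correlation (f=0.32).**

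| rho | N for 95% power, Phase One / Two | Power at 24 / 22 |
|---|---|---|
| 0 | 46 / 34 | 74% / 82% |
| 0.3 | 70 / 64 | 54% / 55% |
| 0.5 | 88 / 82 | 45% / 44% |
| 0.7 | 104 / 102 | 39% / 37% |
| 0.9 | 122 / 120 | 34% / 32% |

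Only a negative correlation would bring the required N down to the stated totals, and that is not plausible for repeated pain scores in the same patient.

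**Step 4: try another routine.** The within-between interaction routine with f=0.32 gives 28 and 24 at rho=0.5, 26 and 22 at 0.52 to 0.55, and 24 and 20 at 0.56 to 0.58. At none of the values tried does it give 24 and 22 together, and it is not the routine the article names.

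**Step 5: compare the test powered with the test described.** The between-factors routine powers the group difference averaged over all time points. The article's list of time points includes pre-intervention, where randomisation implies no difference. I simulated 20,000 trials with no difference at baseline and 0.64 SD at every later point, rho=0.5. Power was about 24% and 27% for the group main effect, and about 33% and 29% for the group-by-time interaction. The interaction figures also depend on rho: about 24% and 22% at 0.3, and 51% and 46% at 0.7.

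**Step 6: check the drop-out allowance.** 24/0.9 = 26.7 and 22/0.9 = 24.4, so 27 and 25, made even as 28 and 26. This part is sound.

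**The case against.** Four points can fairly be made for the plan.

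- **The correlation is unknown.** A reader might infer that the true power is 45%. The documents do not support a single figure. That rho=0.5 returns both totals is good evidence of what was typed into the software, not of how BPI scores will correlate. This stands, and it is why a range is needed.
- **A null result is not shown to be the likelier outcome.** A reader might infer that a non-significant BPI result is more likely than not if d=0.64 is true. That fails at rho=0.5 if all 28 and 26 are analysed (51.5% and 50.8%), and at lower correlations. It also fails for some other analyses: a baseline-adjusted mean of the later time points with a 0.64 SD difference has about 56% and 60% power at N=24 and 22 (rho=0.5). The article mentions an adjusted primary analysis without naming covariates, so neither 45% nor 56% can simply be assigned to it.
- **The label may be the mistake.** The effect size comes from a cited source that is not available here. The article shows only that d and N conflict, so one cannot conclude that f=0.32 is right, or that 88 patients are required.
- **The authors are already cautious.** Phase One is called a pilot. The limitations section concedes that the small samples preclude definitive statements and may lead to type I or II errors. Confidence intervals and Cohen's d are promised. This lowers the risk of over-reading, but does not withdraw or correct the 95% power claim, which is made for both phases.

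**Conclusion.** The point holds as an internal contradiction. For the named routine, an effect of d=0.64, 95% power and totals of 24 and 22 are incompatible at every non-negative correlation. The totals fit f=0.64 at rho=0.5, an effect twice the one written down. If d is right, the required totals are almost four times those stated at rho=0.5 (88/24 = 3.7 and 82/22 = 3.7), and power falls short of 95% by about 13 to 63 percentage points across both phases and rho from 0 to 0.9. If f is right, the power claim is consistent for the test used, but the printed effect size is half the one planned for.

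Separately, the powered test is a main effect that includes the baseline measurement, while the follow-up analysis is built on the interaction. These conclusions rest on the standard formula, 1:1 arms and common variance and correlation. The simulated figures also rest on a constant difference after baseline.

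**What to change.** First confirm against the cited source whether 0.64 is d or f, and correct the label in both phases.

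- **If it is d:** keep the recruited numbers, state the assumed correlation, and remove the 95% power claim. Replace it with the power recomputed for whichever test is the primary analysis, shown over a range of rho. For the named between-factors test that is about 45% and 44% at rho=0.5, with 95% power only for d of about 1.26 and 1.28. Do not carry these figures over to a different or baseline-adjusted test.
- **If it is f:** state that the planning effect is d=1.28, and say why a difference of that size is expected.

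In either case, name the effect being powered (group main effect, interaction or adjusted group difference) so that it matches the primary analysis. Add that a non-significant BPI result will not be read as evidence of no difference between groups, including where it triggers the next step in choosing the Phase Two pressure.

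The cost is a short recalculation and a few sentences. No extra patients are needed. If d is confirmed, the stated power becomes less favourable.

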#### Patient-reported outcome measures

The primary outcome measure of intervention efficacy will be the BPI;^62^ additionally, all participants will be asked to complete the Lower Extremity Function Scale (LEFS).^63^ A detailed description of all PROMs can be found in online supplemental file 4. All other PROMs listed will only be completed based on injury-specific site location. For example, an individual with a foot/ankle injury will only be asked to complete foot/ankle questionnaires, not knee or hip-specific questionnaires.

The BPI is a patient-administered, multidimensional, pain assessment tool commonly used within musculoskeletal clinical practice.^62^ Higher scores on the nine-item short form indicate greater interference with function, or greater pain intensity.^62^ Literature suggests the BPI has excellent test-retest reliability (intra-class correlation coefficient=0.90–0.96) and excellent internal consistency (Cronbach’s α=0.86–0.96) in populations with persistent neuropathic, nociceptive and nociplastic pain.^64^,^66^ The minimally clinically important difference for the BPI is a 2-point reduction for average pain, pain interference and pain severity.^67^,^69^

To assess the feasibility and tolerability of the BFR-RT interventions, a participant monitoring booklet will be used throughout the intervention period (T2_P1_). The booklet consists of multidimensional daily morning well-being questions, training load monitoring (sets × reps × load completed), sessional ratings of perceived exertion, and Numerical Pain Rating Scale (NPRS) for injury-specific pain and localised muscle soreness (NPRS; pre-intervention, immediately post-intervention and 1-hour post-intervention for each BFR-RT session).

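### The 95% power stated for both phases holds only if 0.64 was entered as Cohen's f and repeated BPI scores correlate at no more than about 0.5, a value the protocol does not support

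*Protocol article*

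**What the plan says.** In the Protocol article, the section Sample size calculation describes Phase One as "using a repeated measures analysis of variance (ANOVA; between factors) sample size calculation with an effect size of d=0.64", with power 0.95 and alpha 0.05, and reports: "considering two treatment arms and three measurements timepoints (ie, pre-intervention and post-intervention, and follow-up), the required sample size is 24 patients". Phase Two uses the same routine and effect size with "power=0.95, alpha=0.05, two treatment arms" and four timepoints, and concludes that "the required sample size is 22 patients". Both were "calculated using G Power V.3.1.9.6". After an allowance for 10% dropout, 28 and 26 patients are to be recruited. The article prints no correlation among the repeated measures.

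Under Phase One, Patient-reported outcome measures, the article says of the primary outcome that "the BPI has excellent test-retest reliability (intra-class correlation coefficient=0.90–0.96", citing literature on persistent neuropathic, nociceptive and nociplastic pain. The Figure 1 caption places Phase One's end of intervention on day 5 and its follow-up on day 6. Statistical methods and analysis plans an ANOVA with between- and within-subject factors, and follows up significant two-way interactions.

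**The concern.** In the between-factors routine, extra visits help only so far as they add information that earlier visits did not carry. The more closely a patient's scores track each other, the less each further visit is worth and the lower the power. The printed sizes therefore contain an assumed correlation even though none is stated, and it can be recovered from them. It comes out at about 0.5. The protocol offers nothing in support of a value that low, and the two indications it does give, the cited reliability and the one-day gap between Phase One's last two readings, point higher.

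The stated power matters beyond the sample size section. Under Phase Two, Experimental intervention, the absence of a significant BPI difference in Phase One passes the choice of cuff pressure to the function score, and then to a default. A type II error in Phase One thus feeds into the design of Phase Two. The limitations section concedes that small samples may lead to type I or II errors, yet the sample size section states 95% without qualification.

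**Working it through.** **Inputs.** From Sample size calculation: two arms, alpha 0.05, power 0.95, effect size 0.64; m=3 timepoints and N=24 (Phase One), m=4 and N=22 (Phase Two); recruited N 28 and 26. Allocation is 1:1 (Randomisation and blinding procedure). Assumption: the correlation r among visits is not printed, so it is varied.

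**Formula (between-factors main effect).** Noncentrality λ = N·f²·m / (1 + (m−1)·r), referred to a noncentral F with 1 and N−2 degrees of freedom.

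**Reproducing the plan.** With f=0.64, f²=0.4096, and r=0.5:
- Phase One: λ = 24 × 0.4096 × 3 / 2 = 14.75; power 95.6%; smallest even N = 24.
- Phase Two: λ = 22 × 0.4096 × 4 / 2.5 = 14.42; power 95.05%; smallest even N = 22.

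The routine returns exactly 24 for r from about 0.44 to 0.535, and exactly 22 for r from about 0.42 to 0.50. A value of 0.5 fits both. Lower correlations give more power, so 0.535 and 0.50 are ceilings rather than required values.

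**Taking the label literally.** For two equal arms f = d/2, so d=0.64 is f=0.32. Then r=0.5 needs 88 and 82 patients. Even r=0 needs 46 and 34, so no non-negative correlation yields 24 and 22.

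**Varying r with f=0.64.**

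| r | Phase One, N=24 | Phase One, N=28 | Phase Two, N=22 | Phase Two, N=26 | N for 95% (One / Two) |
|---|---|---|---|---|---|
| 0.5 | 95.6% | 97.9% | 95.0% | 97.7% | 24 / 22 |
| 0.6 | 93.8% | 96.7% | 92.7% | 96.2% | 26 / 26 |
| 0.7 | 91.8% | 95.4% | 90.0% | 94.5% | 28 / 28 |
| 0.8 | 89.6% | 93.8% | 87.2% | 92.4% | 30 / 30 |
| 0.9 | 87.3% | 92.1% | 84.3% | 90.2% | 32 / 32 |
| 0.96 | 85.9% | 91.0% | 82.6% | 88.8% | 34 / 34 |

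For example, at r=0.9: λ = 29.49 / 2.8 = 10.53 (Phase One) and 36.04 / 3.7 = 9.74 (Phase Two).

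**The fourth visit.** The factor m/(1+(m−1)r) is 1.50 for three visits and 1.60 for four at r=0.5, but 1.07 and 1.08 at r=0.9. From r=0.6 upward both phases need the same N, so the reduction from 24 to 22 is a product of the assumed correlation.

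**Varying r with f=0.32.** Power at 24/22 is 45%/44% at r=0.5 and 34%/32% at r=0.9.

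**Interaction, for contrast.** For group-by-time, λ = N·f²·m/(1−r), with m−1 and (N−2)(m−1) degrees of freedom under sphericity. With f=0.32 used for illustration, N=24 and m=3, λ = 24 × 0.1024 × 3 / 0.5 = 14.75 at r=0.5, power 92%. At r=0.9, λ = 73.7 and power is close to 100%. The direction is reversed.

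**The case against.** A reader might infer that visits in this trial correlate at 0.90–0.96, so that true power is 83–87% and the two sections contradict each other. The documents do not support that. The coefficient is cited literature on test-retest agreement in other pain populations, given to vouch for the instrument. The input needed here is the correlation across visits in treated patients with mixed diagnoses, who may respond differently. In Phase One, two of the three visit pairs span the intervention; only the day 5 and day 6 pair resembles a retest. The cited range is therefore an upper bound.

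The 83–87% also applies only at 24 and 22, which means losing 4 of 28 (14%) and 4 of 26 (15%), more than the planned 10%. With no loss, power at 0.90–0.96 is about 89–92%, and at 0.7 the target is met or nearly met.

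A reader might also infer that a high correlation is harmful whichever effect is tested. It is not: for the group-by-time interaction that the analysis section follows up, a higher correlation raises power.

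Finally, leaving a software input out of a condensed article is not a fault. All of this stands. What remains is that the 95% is a printed figure tied to a named test, and for that test it depends on a correlation that the protocol gives no reason to expect.

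**Conclusion.** The point holds as a limited one. If 0.64 is taken as Cohen's f, the between-factors test has the stated 95% power at 24 and 22 only for a correlation of at most about 0.535 and 0.50. Phase Two has no margin above 0.5. At moderate correlations of 0.6 to 0.7 the shortfall is about 1 to 5 percentage points at the required N, and the dropout allowance largely absorbs it if few patients are lost. At 0.9 it is about 8 and 11 points at the required N, and about 3 and 5 points at the recruited N.

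The effect-size entry is the larger error. As printed (d=0.64), power is below one half in both phases even at 0.5, and a higher correlation lowers it further.

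These results assume the between-factors main effect with equal correlation between all visits. They do not show that 0.5 is wrong for this trial, because the documents give no visit-to-visit correlation. They show that the unqualified 95% rests on an unsupported value.

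**What to change.** Keep both recruitment targets. In Sample size calculation:
- Name the effect being powered (between-group main effect or group-by-time interaction) and state the assumed correlation among repeated BPI scores.
- State whether 0.64 is d or f, and enter it accordingly.
- Replace the single 95% with power for that effect over a plausible range of correlations, for example 0.5 to 0.9, at both the required and the recruited N.
- Do not present the fourth visit as reducing the number of patients needed.

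Before Phase Two opens, take the pooled, arm-blind SD and visit-to-visit correlation of the BPI from Phase One, which shares its site, eligibility criteria and instrument. Use them to restate Phase Two's power or detectable difference.

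The cost is a rewording and one further calculation. No extra patients are needed, but the stated power becomes less favourable.
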